#### Following years (August 2014 – May 2017)

In the consecutive years, while procedure for data collection (at CHCs) remains unchanged across the three arms, preschools in the Universal and Universal Plus arms will start the dissemination of the interventions. Preschools in the Universal arm will only offer Triple P Seminar Series plus the short individual counselling within level 2. Preschools in the Universal Plus arm will offer Triple P Seminars as well as Triple P Primary Care and Triple P Group.

All three levels of intervention will be advertised for parents of 3- to 5-year-old children, but they will be open to all parents. Targeted parents are free to accept or decline the offer. We expect about 30 to 40% of the families in both intervention arms to attend at least one of the seminar sessions. We expect the uptake of the Primary Care and Group Triple P to be between 10 to 20% in the Universal Plus arm.

### Analytic plan

#### Population level analysis

A key question in the study pertains to evaluating the impact of the intervention arms at the level of the preschool, i.e. at a population level. This analysis will examine how the intervention conditions impact aggregate children’s social-emotional and behavioural health as reported by parents and preschool teachers. Mean level scores are of interest, as well as proportion of children above the clinical cut-off on the instrument. The baseline year will include all children ages 3–5 in the preschools. The second year will again include all children 3–5 years of age in the preschools, with only the continuing 4-year-olds and 5-year-olds having been assessed in the baseline year. Similarly, the third year, which again will include all children 3–5 years of age in the preschools, but with only the continuing 5-year-olds having been assessed in the two prior years. Focusing only on aggregate effects at the level of the preschool, ANCOVA will be conducted with the three arms, controlling for baseline and other preschool-level covariates (e.g. socioeconomic level).

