#### Preschools

There are 13 preschool administrative areas in Uppsala municipality. The preschool leadership in the municipality accepted to participate in the project. It was agreed that the administrative areas would be randomised into the three arms of the study with all preschools within an area automatically belonging to the allocated arm of that area.

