### Allocation

Allocation was performed through randomising the 13 areas into the three arms of the study. The randomisation was conducted by the preschool leadership at one of their team meetings. Names of all the areas were written on pieces of papers and put in a container. Thereafter, consecutive allocation to groups 1, 2 and 3 took place as the pieces of paper were drawn from the container, where group 1 was the Universal Plus arm, group 2 the Universal arm and group 3 the Services as Usual arm. Four persons witnessed the randomisation process and no changes in allocation were made after the draw. Five areas were allocated to the Universal Plus arm, four to the Universal arm and four to the Services as Usual arm. Individual preschools in each area automatically belonged to the allocated arm for that area.

Because the trained practitioners will not necessarily have to work at the allocated preschools, the intervention preschools will not need to send their own personnel for training, but will be served by practitioners from other preschools. Similarly, preschool teachers with previous Triple P training who work at preschools in the control areas will not be allowed to deliver Triple P in their own preschools. The training costs will be covered by the research grant, whereas implementation costs will be covered by the municipality.

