#### Longitudinal analysis

The design also permits examination of how individual children (nested within preschools) progress longitudinally with respect to outcome measures, as a function to intervention exposure. Specifically, children who are age 3 years during the baseline year will be followed longitudinally through the second and third years (i.e. from age 3 to age 5). Similarly, the children who are age 4 years during the baseline year will be followed longitudinally through the second year. Hierarchical linear modelling, which will account for clustering, will be used to test the effects of intervention conditions, controlling for baseline and other covariates. Assuming an alpha of .05 and 80% power, it is estimated that the design as planned permits detection of effect sizes ranging from .17 for an intraclass correlation of 0.02 to .26 for an intraclass correlation of 0.10. The study is powered to detect small to moderately small effects.

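### The population-level ANCOVA takes the preschool as its unit although 13 areas were randomised, so it overstates precision whenever area-level variance remains after adjustment

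*Protocol article*

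**What the plan says.** **Allocation.** Under Allocation: "Allocation was performed through randomising the 13 areas into the three arms of the study". The result is "Five areas were allocated to the Universal Plus arm, four to the Universal arm and four to the Services as Usual arm". Under Recruitment process, Preschools, the areas were randomised "with all preschools within an area automatically belonging to the allocated arm of that area". No preschool was drawn separately.

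**Population-level test.** Under Analytic plan, Population level analysis: "Focusing only on aggregate effects at the level of the preschool, ANCOVA will be conducted with the three arms". The adjustment described there is for the baseline value and for covariates measured on the preschool, with socioeconomic level as the example. The section calls this a key question. It does not mention the area.

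**Longitudinal test.** Under Longitudinal analysis, the subject is "how individual children (nested within preschools) progress longitudinally", and "Hierarchical linear modelling, which will account for clustering, will be used to test the effects of intervention conditions". Detectable effects of 0.17 at ICC 0.02 and 0.26 at ICC 0.10 are given for alpha 0.05 and 80% power. The text does not say which level the ICC refers to, how many clusters there are or how large they are.

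**The concern.** Treatment varies only between areas, so the error against which an arm contrast is judged must include the variation between areas. An ANCOVA on preschool values treats every preschool as an independent draw. If areas differ in ways that the covariates do not capture, preschools in one area are correlated. The model's residual then understates the variance of an arm mean, and the test takes its degrees of freedom from the number of preschools instead of the 13 areas.

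At stake are the confidence intervals and p-values of every arm contrast in the population-level analysis. With four or five areas per arm, chance differences between areas could be declared programme effects more often than the nominal 5%.

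**Working it through.** **1. Degrees of freedom.** 13 areas − 3 arms = 10 error df before covariates, or 9 with one baseline covariate. The article gives no number of preschools. With an assumed 8 per area there are 13 × 8 = 104 preschools, and a preschool-level ANCOVA would use 104 − 3 = 101 before covariates.

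**2. Which clusters fit the stated detectable effects?** Take d = (1.960 + 0.842) × √[(2/k) × (ICC + (1 − ICC)/m)], with k clusters per arm, m children per cluster and two-sided alpha (assumed). The two stated pairs give two equations in k and m. The solution is k ≈ 31 and m ≈ 26. Forward check:
- ICC 0.02: 2.802 × √[(2/31) × (0.02 + 0.98/26)] = 0.171
- ICC 0.10: 2.802 × √[(2/31) × (0.10 + 0.90/26)] = 0.261

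Allowing for rounding, the pairs fit 28–35 clusters per arm, a number that suggests preschools. Four or five areas per arm reproduce the pair only if an unstated area-level covariate R² of about 0.86–0.91 is assumed.

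**3. The same effects on areas.** With 5 v 4 areas, no covariate gain and unlimited children per area, d ≥ 2.802 × √[(1/5 + 1/4) × ICC]:
- ICC 0.02: 2.802 × √0.009 = 0.27 (stated 0.17)
- ICC 0.10: 2.802 × √0.045 = 0.59 (stated 0.26)

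For 4 v 4 areas the floors are 2.802 × √0.010 = 0.28 and 2.802 × √0.050 = 0.63. With 200–588 children per area and t-based tests, power at the stated effects is about 25–32% (0.17) and 16–18% (0.26). These figures apply the stated ICCs at area level; a smaller area ICC would give smaller detectable effects.

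**4. Type I error of the preschool-level ANCOVA.** Simulated with no treatment effect. From the article: 13 areas split 5/4/4. Assumed: 8 preschools per area, 25 children each, preschool ICC 0.03, baseline as the only covariate, and a baseline-to-follow-up correlation of cluster effects of 0.6 or 0.9. Where a range is shown, it covers these two correlations.

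| Area ICC (assumed) | Rejection rate, three-arm F test, nominal 5% |
|---|---|
| 0 | about 4% (nominal within simulation error) |
| 0.001 | 5.5–7% |
| 0.005 | 10–11% |
| 0.01 | 13–18% |
| 0.02 | 19–26% |

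An ANCOVA on the 13 area means stays at 4–6% throughout.

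**5. Effect of the planned socioeconomic covariate.** A separate set of runs at correlation 0.6 gave 11%, 18% and 29% at area ICC 0.005, 0.01 and 0.02 without the covariate. If it explains half of the area variance (assumed), these fall to 8%, 11% and 18%. If it explains 80%, they fall to 6.5%, 7.5% and 10%.

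**The case against.** Three points on the other side have weight.

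**The longitudinal model.** A reader might infer that both planned analyses leave out the area. The documents do not support that. The mention of preschools describes the children and is not a list of model levels. The text says clustering will be accounted for, and an area level is neither stated nor excluded. The article is condensed, and random-effects detail is commonly left to a full analysis plan. The back-solved 31 clusters per arm point towards preschools, but they are not unique evidence and concern the power statement rather than the fitted model. This objection stands in full for the longitudinal analysis. It does not help the ANCOVA, whose unit is stated.

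**The size of the inflation.** A reader might also infer that false-positive rates are known to be far above 5%. The article gives no area-level ICC, number of preschools or preschool size. With no residual area variance there is no inflation, and baseline and socioeconomic adjustment may remove much of it. This stands: the size is conditional. But nothing in the article justifies taking the residual area variance as zero.

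**Bias.** It would be wrong to say that area differences bias the estimated effect. Under random allocation, omitting the area leaves the estimate unbiased and understates its variance.

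**Conclusion.** The point holds for the population-level ANCOVA. As written, the test of a key question uses a unit that was not randomised and has no term for the one that was. Its precision is overstated whenever area variance remains after adjustment. On the assumptions in the working, the inflation is negligible at an area ICC of 0.001 or less. At 0.01–0.02 with baseline adjustment only, the rejection rate is roughly two and a half to five times nominal, and less if socioeconomic level explains part of the area differences.

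For the longitudinal model the conclusion is narrower: the text should say whether area is a level. The detectable effects printed there do not fit 13 areas unless a very large covariate gain is assumed.

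**What to change.** Base the test of arm effects on the randomised unit. Either of these will do:
- a child-level mixed model with fixed effects for arm, baseline and the planned covariates, random effects for area and for preschool within area, and Kenward-Roger or Satterthwaite degrees of freedom; or
- an ANCOVA on the 13 area summaries.

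A permutation test over the 13!/(5! 4! 4!) = 90,090 possible allocations is an optional check. Name area as a level in the longitudinal hierarchical model as well. Recalculate the detectable effects on 13 areas, stating the area-level ICC and any covariate gain assumed.

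The change needs only analysis wording, because each preschool's area already determines its arm. The price is wider confidence intervals and a less favourable detectable effect: at least about 0.27 and 0.59 for 5 v 4 areas at the stated ICCs without covariate gain, against 0.17 and 0.26.

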#### Longitudinal analysis

The design also permits examination of how individual children (nested within preschools) progress longitudinally with respect to outcome measures, as a function to intervention exposure. Specifically, children who are age 3 years during the baseline year will be followed longitudinally through the second and third years (i.e. from age 3 to age 5). Similarly, the children who are age 4 years during the baseline year will be followed longitudinally through the second year. Hierarchical linear modelling, which will account for clustering, will be used to test the effects of intervention conditions, controlling for baseline and other covariates. Assuming an alpha of .05 and 80% power, it is estimated that the design as planned permits detection of effect sizes ranging from .17 for an intraclass correlation of 0.02 to .26 for an intraclass correlation of 0.10. The study is powered to detect small to moderately small effects.

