### Aims

The aim of this paper is to provide a detailed study protocol of a controlled preschool randomisation trial, including 7,600 children. The aim of the Children and Parents in Focus trial is to compare two levels of programme intensity and rate of exposure, with a control condition to address impact and cost-effectiveness of a universally offered evidence-based parenting programme in the Swedish context of preventive services.

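### The stated detectable effects (.17 to .26) are not supported by the 13 randomised areas unless strong assumptions that the protocol does not state are made

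*Protocol article*

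**What the plan says.** The power statement stands under Longitudinal analysis in the Analytic plan. Its premise is given as "Assuming an alpha of .05 and 80% power". On that basis the article estimates that the trial "permits detection of effect sizes ranging from .17 for an intraclass correlation of 0.02 to .26 for an intraclass correlation of 0.10". The conclusion drawn is that "The study is powered to detect small to moderately small effects". The same section describes the analysis as one of "how individual children (nested within preschools) progress longitudinally", using a hierarchical linear model that adjusts for baseline and other covariates. It gives no number or size of clusters, no level for the ICC and no R².

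The Allocation section fixes the randomised unit: "Allocation was performed through randomising the 13 areas into the three arms of the study". The split is explicit: "Five areas were allocated to the Universal Plus arm, four to the Universal arm and four to the Services as Usual arm". Preschools were not randomised individually: "Individual preschools in each area automatically belonged to the allocated arm for that area". The Aims section nevertheless calls the study a "controlled preschool randomisation trial, including 7,600 children".

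**The concern.** In a cluster-randomised trial, precision is governed mainly by the number of randomised units per arm. Here that is four or five. With so few clusters, an ICC between .02 and .10 at the level of randomisation leaves a between-cluster variance that extra children cannot reduce. Effects of .17 and .26 look too small for such a design. The ratio between the two figures also points to small clusters, of preschool rather than area size.

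What is at stake is how a null result would be read. The Introduction notes that universally offered programmes have so far shown small effects. The section on the following years expects 30 to 40% of families to attend at least one seminar, so a small population effect is plausible. If the power statement is taken at face value, a null result would be read as evidence against such effects when the trial may have had little chance of detecting them.

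**Working it through.** **Inputs**
- Alpha .05 (two-sided assumed; sidedness is not stated), power 80%, and the pairs .17 at ICC .02 and .26 at ICC .10: Longitudinal analysis.
- 13 areas, 5/4/4: Allocation.
- Children per area, from the counts under Recruitment process. The longitudinal cohort is those aged three and four at baseline: 2,603 + 2,494 = 5,097, and 5,097/13 ≈ 392. All children: 7,638/13 ≈ 588. Both are upper bounds that assume full participation.

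**Formula.** For two arms with J₁ and J₂ clusters of n children, the detectable standardised effect is

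d = M × √{(1/J₁ + 1/J₂) × [ICC(1 − R²_cluster) + (1 − ICC)(1 − R²_child)/n]}

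Here M is 2.80 (1.96 + 0.84) under the normal approximation and 3.11 with a noncentral t on 10 df (13 areas − 3 arms).

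**Step 1: what reproduces the stated pair without covariates.** Set R² = 0 and k clusters per arm:
- (.17/2.80)² = .00368 = (2/k)(.02 + .98/n)
- (.26/2.80)² = .00861 = (2/k)(.10 + .90/n)

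Dividing the second by the first removes k: (.10 + .90/n)/(.02 + .98/n) = 2.34, so n ≈ 26.2. Then k ≈ 31.2. That is about 94 clusters and 2,450 children over three arms. Allowing for rounding of the two effects, k is about 28 to 35 and n about 21 to 34. As a check, k = 31 and n = 26 give .171 and .261.

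**Step 2: the randomised areas, no covariates, stated ICCs applied at area level.** For 5 versus 4 areas, 1/5 + 1/4 = .45. With n = 392:
- ICC .02: .02 + .98/392 = .0225; d = 3.11 × √(.45 × .0225) = .31
- ICC .10: .10 + .90/392 = .1023; d = 3.11 × √(.45 × .1023) = .67

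| Comparison, 10 df | ICC .02 | ICC .10 |
|---|---|---|
| 5 vs 4, n = 392 | .31 | .67 |
| 5 vs 4, n = 588 | .31 | .66 |
| 5 vs 4, n unlimited | .295 | .66 |
| 4 vs 4, n = 392 | .33 | .70 |
| Protocol | .17 | .26 |

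Power at the stated pairs (5 vs 4, n = 392) is about 33% for .17 at ICC .02 and about 20% for .26 at ICC .10. Choosing other conventions does not close the gap. With unlimited children and a normal approximation, 5 versus 4 gives .27 and .59. One-sided testing gives .24 and .53. Pooling both intervention arms (9 versus 4) one-sided gives .21 and .47.

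**Step 3: baseline adjustment (5 vs 4, 10 df, n = 392 to 588).**
- R² = .5 at both levels: about .22 and .47.
- R² = .7 at area level only: about .18–.19 and .37.
- R² = .7 at both levels: about .17 and .37. The lower figure is reached; the upper is not.

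Solving for the area-level R² that gives both stated figures yields .86 (5 vs 4, normal), .88 (5 vs 4, 10 df) and .91 (4 vs 4, 6 df). It also needs n/(1 − R²_child) of about 184–292. That is below the 392 children of a full longitudinal cohort, so it also implies incomplete participation and little child-level gain from baseline.

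**Step 4: a smaller ICC at area level.** Without covariates, and with n = 392 to 588, .17 is reached at an area-level ICC of about .004–.005, and .26 at about .013–.014.

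**The case against.** The strongest reply is that the model adjusts for baseline, as stated in the sentence just before the power statement, whereas the back-solve in Step 1 sets R² to zero. This stands as far as it goes. With R² of .5 at both levels the back-solved number falls to 15.6 clusters per arm, and with .7 to 9.4. With an area-level R² near .9, the 13 areas themselves roughly reproduce the pair. So a reader who infers that the figures can arise only from about 30 clusters per arm goes too far: that holds only without adjustment. What adjustment does not do, at the more moderate R² values tried, is bring down the upper figure, which stays at about .37 or more against .26.

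A second reply is that the ICCs may be preschool-level values, since preschools are the only nesting level named, and that the area-level ICC could be much smaller. This also stands, and it means that .31–.67 is conditional. It does not rescue the statement as written, because the power claim would then rest on an ICC for a unit that was not randomised.

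Third, it is tempting to say that the calculation treated preschools as the randomised unit. The cluster size of about 26 and the wording of the Aims suggest it, but the article gives neither the number of preschools nor the formula. Solving two figures for two unknowns always returns some answer, so this remains an inference. A condensed article may also leave such inputs to the full protocol. The finding is not that they are absent but that the stated figures do not fit the stated allocation.

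**Conclusion.** The power statement is wrong as written for the design described. With 5 versus 4 areas, 10 df, about 392 children per area, no covariates and the stated ICCs at area level, the detectable effects are about .31 and .67 (4 versus 4: .33 and .70), roughly 1.8 and 2.6 times those stated (.31/.17 and .67/.26). Plausible baseline adjustment may bring the lower figure close to .17, but the upper one remains at about .37 to .47 for R² between .5 and .7. The stated pair requires either near-complete removal of between-area variance (R² about .86–.91) or area-level ICCs well below those quoted, and neither is stated.

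Two stronger conclusions are not supported. One is that .31–.67 is what this trial can detect: that range depends on the ICC level and ignores adjustment. The other is that small effects were beyond its reach: with good adjustment and an ICC near .02, effects of about .2 could be detectable. Confidence is high in the mismatch between the power figures and the randomised units. It is lower on its cause and on the values that should replace them.

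**What to change.** Recompute the detectable effects with the 13 randomised areas (5/4/4) as clusters and about 10 df, using the expected size of the longitudinal cohort. State the level to which the ICC refers, its range, and the baseline R² assumed at area and child level. Report the result with and without adjustment. If ICCs of .02–.10 are held to apply at area level, the unadjusted entry would be about .31–.67; if a smaller area-level ICC is assumed, state it with its basis.

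Replace .17–.26 with the result, and requalify the sentence claiming power for small to moderately small effects so that it carries the same assumptions. The cost is one rewritten paragraph and no additional participants. The downside is a less favourable stated figure.

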#### Cost-effectiveness analysis

Economic evaluation will be presented first as a cost-consequences analysis [34], which allows policy makers to compare the incremental costs with all outcomes of interest – i.e. child behaviour, parent’s mental health, etc. and impact on parent’s health-related quality of life. Economic evaluation will then present cost-effectiveness analyses, comparing incremental costs to incremental changes in child behaviour and a cost-utility analysis, comparing incremental costs to incremental parental quality of life (as measured by GHQ12 transformed to EQ-5D). The results of the analysis will be expressed as *incremental cost-effectiveness ratios* (ICER) [35] where differences in costs are compared to differences in health consequences (Δcost/ΔQALY) for each intervention.

A decision analytical model will be developed to perform long-term prognostic calculations of potential health effects and costs savings due to reduction of child mental health problems. Analyses of long-term cost-effectiveness of early intervention will be provided.

## Discussion

The preschool years constitute one of the most sensitive periods in a child’s development and several early intervention strategies are available. There is a paucity of research on the long-term effects of structured parenting programmes offered to the population at large. Sweden has a tradition of universal parenting education through individual contact, but the effects of specific interventions are seldom evaluated within the system. Health economic evaluations are imperative for decision makers, but most parenting interventions lack such data. If Sweden is to keep using its resources in an equitable and cost-effective way, while keeping its international forefront position, it is time to empirically develop an effective blend of culturally appropriate interventions to change the prevalence of child mental health problems.

This study addresses the need for comprehensive evaluation of the long-term effects, costs and benefits of early parenting interventions embedded within existing systems. In addition, the study will generate population-based data on the mental health and well-being of preschool aged children in Sweden as currently, there is almost no such data available [5].

